### Sample size calculation

Based on a previous proof-of-principle RCT,^4^ a sample size of n=120 participants is necessary to have 80% power (α=0.05) to detect a between-group difference of d=0.30 of the primary outcome (PTSD symptoms at 6 weeks). Furthermore, we calculated the sample sizes necessary to obtain significant group differences with 80% power (α=0.05) based on small effect sizes (d<0.30) for maternal secondary outcomes (PTSD diagnosis, ASD symptoms and physiological stress reactivity) and infant secondary outcomes (physiological stress reactivity) based on small effect sizes (d<0.30) with 80% power (α=0.05), which range between a total of n=56 and n=84. Predicting a 20% drop-out rate, we aim to recruit 144 women.

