The allocation ratio of randomisation is 1:1. The randomisation sequence will be generated using a computer-generated block randomisation (StataCorp 2017. Stata Statistical Software: Release 15) using blocks of sizes 2, 4 and 6 over 144 participants per stratum (stratified by research centre). Opaque envelopes will be prepared in advance, numbered sequentially by alternating between stratums by block. After conducting the baseline assessment, the clinical midwife/nurse will open the envelope and announce the cognitive task to be carried out (ie, the cognitive visuospatial task or the attention-placebo control task) to the participant.^95^ All members of the research group as well as participants are blind to group allocation. All participant data will be coded to ensure confidentiality. After completing the 15 min cognitive tasks, both women of the control and intervention group will complete the same assessments, as shown in table 1; see figure 1 for an overview of the study variables.

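### The stated 80% power for d=0.30 with 120 women is wrong for the planned comparison (about 37% unadjusted), and the basis of the secondary-outcome sizes is not stated

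*Protocol article*

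**What the plan says.** The section 'Sample size calculation' of the protocol article gives sample size, effect, alpha and power for the primary outcome in one sentence: "a sample size of n=120 participants is necessary to have 80% power (α=0.05) to detect a between-group difference of d=0.30 of the primary outcome". It cites an earlier proof-of-principle trial as the basis. It does not say whether the test is one- or two-sided, and gives no baseline correlation.

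For PTSD diagnosis, acute stress symptoms, and maternal and infant stress reactivity, the same section gives sample sizes "based on small effect sizes (d<0.30) with 80% power (α=0.05), which range between a total of n=56 and n=84". It closes with "Predicting a 20% drop-out rate, we aim to recruit 144 women".

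The design facts that enter the calculation are elsewhere in the article:

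- **Allocation** ('Study population, recruitment, group allocation and blinding'): "The allocation ratio of randomisation is 1:1".
- **Primary analysis** ('Data management and statistical analyses'): separate linear regressions of CAPS-5 and PCL-5 scores at 6 weeks, adjusted for centre, baseline values and any covariates found significant.
- **Secondary aims** (same section): group differences at time points and group differences in change; logistic regression for PTSD diagnosis.

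**The concern.** A standardised difference of 0.30 is small, and a two-group trial of 120 is usually too small to detect it with 80% power. If the stated power is wrong, the only justification given for the size of a phase III trial is wrong. Readers who later meet a non-significant primary result may also weigh it as though the trial had an 80% chance of finding d=0.30.

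The secondary sentence raises a further question. It pairs effects below 0.30 with fewer women than the primary effect of 0.30, at the same alpha and power. For comparisons of the same kind, a smaller effect needs more women.

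**Working it through.** **Inputs.** d=0.30, alpha 0.05, power 80%, total 120, 20% drop-out and 144 recruited ('Sample size calculation'); 1:1 allocation; two independent groups compared at 6 weeks. Two-sided testing is my assumption; one-sided is also tried.

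**1. Trying to reproduce 120.** Per arm, n = 2(z₀.₉₇₅ + z₀.₈₀)²/d² = 2(1.960 + 0.842)²/0.30² = 2 × 7.849/0.09 = 174.4, so 175 per arm and 350 in total. The exact two-sample t test gives 175.4 per arm, or 351 in total. The stated 120 is not reproduced.

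**2. Power with 120 (60 per arm).** Normal approximation: 0.30 × √(60/2) − 1.960 = 1.643 − 1.960 = −0.317, and Φ(−0.317) = 37.6%. The exact t test gives 37.1%. Its detectable effect at 80% power is d=0.52.

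**3. Power after the planned drop-out.** 144 × 0.80 = 115.2, so about 115 analysed: power for d=0.30 is 36%, and the detectable effect is d=0.53. The figure 144 is 120 × 1.2; to retain 120 after 20% loss takes 120/0.80 = 150.

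**4. Other readings of the primary figure.**

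| Reading | Result |
|---|---|
| One-sided alpha 0.05 | 276 needed; about 50% power at 120 |
| 120 per arm | 64% two-sided, 75% one-sided; conflicts with 144 in total |
| All 144 analysed | 43% |
| Cohen's f=0.30 | about 90 needed |
| Correlation r=0.30 | about 85 needed |
| Paired t test, d=0.30 | about 90 needed |

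None gives 120.

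**5. Covariate adjustment.** With covariate-outcome correlation ρ, the required N is multiplied by (1 − ρ²). For 120 to suffice, ρ = √(1 − 120/350) = 0.81 (one-sided: √(1 − 120/276) = 0.75). Over assumed two-sided values of ρ:

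| Assumed ρ | Power at 120 for d=0.30 |
|---|---|
| 0 | 37% |
| 0.3 | 40% |
| 0.5 | 47% |
| 0.7 | 63% |

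Table 1 marks the maternal CAPS-5 and PCL-5 only at 6 weeks and 6 months, so neither scale has an earlier value to adjust for.

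**6. Secondary sizes as single-time two-group comparisons (t test).**

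| Total N | Power at d=0.30 | d with 80% power |
|---|---|---|
| 56 | 20% | 0.76 |
| 84 | 27% | 0.62 |

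Below d=0.30 the power is lower still.

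**7. Secondary sizes as repeated-measures interactions.** Take f = d/2 = 0.15 for the group-by-time interaction, m measurements with common within-person correlation ρ, noncentrality λ = f²Nm/(1 − ρ), and degrees of freedom m − 1 and (N − 2)(m − 1). For m=2, ρ=0.7, N=56: λ = 0.0225 × 56 × 2/0.3 = 8.4 on 1 and 54 degrees of freedom, which gives 80% power.

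| Measurements | Assumed ρ | Total N for 80% power |
|---|---|---|
| 2 | 0.7 | 56 |
| 3 | 0.5 | 74 |
| 4 | 0.5 | 62 |
| 7 | 0.3 | 62 |

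The correlations and the effect convention are my assumptions; the article states neither. All four results lie within 56 to 84.

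**The case against.** The primary figure has no defence from the stated inputs. The best available one is covariate adjustment: the model adjusts for baseline values, and the acute stress, anxiety and depression scales are taken within 6 hours of the birth and may be prognostic. That stands to the extent that 37% is an unadjusted figure and must be labelled so. It does not rescue 80%, which needs a correlation near 0.81 that the article neither states nor supports.

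A reader might infer that the secondary sizes are further off than the primary one, or that the sentence contradicts itself. The article does not support this. Secondary aims are analysed partly as differences in change, and several of the outcomes are repeated: maternal cortisol seven times and infant cortisol three times around the stressor, and the acute stress scale at two visits. Step 7 shows that such designs can need 56 to 74 women at a nominally equal effect. What remains is that the sentence labels its effects as d and names no design that would make the sizes right. This defence also does not reach PTSD diagnosis, which is binary. Nor does the article say which outcome goes with which size, so a detectable proportion cannot be attached to n=84.

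A reader might also infer that a null primary result could never exclude d=0.30. That depends on the observed interval. With 60 per arm the 95% half-width is about 1.96 × √(2/60) = 0.36 in SD units, so an estimate of 0.10 in favour of control would have an upper limit of about 0.26 in favour of the intervention, which excludes 0.30.

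The source calculation is cited but not shown, so how 120 arose is unknown.

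**Conclusion.** The primary claim is wrong as written. For the planned comparison, 120 women are about a third of the 351 that d=0.30 needs. Unadjusted power is 37% with 120 analysed and 36% with the 115 left after the planned drop-out, against a stated 80%. This rests on two-sided testing, equal arms and no covariate gain; one-sided testing, or assumed correlations up to 0.7 with two-sided testing, still leave power below 80%.

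For the secondary outcomes the supportable conclusion is narrower: the stated sizes cannot have 80% power as single-time comparisons, and the text does not give the design under which they could.

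The finding does not show that the trial should recruit 351 women, or that a null result is to be expected. It shows that the power statement should not be used to interpret one.

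**What to change.** Keep the recruitment target and correct the statement. For the primary outcome, for example: *Recruiting 144 women and allowing for 20% drop-out leaves about 115 analysed, which gives 80% power (two-sided alpha 0.05, unadjusted) for d=0.53; power for d=0.30 is about 36%.* If 120 analysed is kept as the reference, the matching figures are d=0.52 and 37%. If the source calculation used another effect metric or an assumed covariate correlation, name it, justify it and convert the effect to d.

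For the secondary outcomes, give the design, effect metric and within-person correlation behind each size, and state PTSD diagnosis as detectable proportions. Writing d=0.76 to 0.62 in place of the current text would be right only if these were single-time comparisons.

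Add that a non-significant primary result will be interpreted from its confidence interval, not from the planned power.

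The cost is wording and a less favourable stated figure; no additional women are recruited.

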### Study population, recruitment, group allocation and blinding

All women, who have an ECS ≥34 weeks gestation, give birth to a live baby, and give written consent are eligible to participate. In addition, they have to answer with a score of ≥2 separately for at least two out of four screening questions regarding perceived threat.^94^ All screening questions are answered on a 7-point Likert scale (1=not at all, 7=extremely): Did you think that your life was in danger? Did you think that your baby’s life was in danger? Did you feel frightened during the birth? Did you feel helpless during the birth?

Exclusion criteria include: established intellectual disability or psychotic illness, insufficient French-speaking level to participate in assessments, severe illness of mother or infant (eg, cancer, cardiovascular disease, severe neurodevelopmental difficulties and malformations) or if the infant requires intensive care, and alcohol abuse and/or illegal drug use during the pregnancy.

Following an ECS and once the mother has sufficiently recovered, the mother’s midwife/nurse will assess eligibility and if eligible, will inform the mother about the study. After providing written and informed consent to be screened, participants will be screened immediately for perceived threat of the mother and/or child with four screening questions. If participants score ≥2 separately for at least two out of the four questions, they will be randomly assigned to either the intervention or attention-placebo control group. We aim to recruit 144 women and their infants (see the Sample size calculation section).

If the woman agrees, then the partner will also be informed about the study. Inclusion criteria for the partners are that they were present at the childbirth and give written consent. Partners are excluded if they do not speak French sufficiently well to participate in assessments. All participants will be reimbursed for their time and effort.

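### The target of 144 inflates 120 by 20% instead of allowing for a 20% loss: about 115 women would have primary-outcome data, not 120

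*Protocol article*

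**What the plan says.** The Sample size calculation section of the protocol article states for the primary outcome that "a sample size of n=120 participants is necessary", at 80% power and α=0.05, "to detect a between-group difference of d=0.30 of the primary outcome (PTSD symptoms at 6 weeks". It gives smaller totals, 56 to 84, for the secondary outcomes it sized, so 120 is the number that drives recruitment. The section closes with "Predicting a 20% drop-out rate, we aim to recruit 144 women".

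The section on study population and recruitment repeats the target: "We aim to recruit 144 women and their infants (see the Sample size calculation section". The abstract and the randomisation paragraph also use 144. Allocation is equal between the arms: "The allocation ratio of randomisation is 1:1". The statistical analysis section adds that missing data may be handled by multiple imputation where appropriate. The article describes the 20% only as predicted drop-out and does not tie it to a visit.

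**The concern.** The section prints three figures (120 needed, 20% lost, 144 recruited) that do not agree. The allowance was made by adding 20% of the required number, whereas the loss applies to the larger number recruited. Under the plan's own prediction the trial therefore ends below the size it calls necessary.

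At stake is the expected number of primary outcomes and the loss the trial can absorb. A reader or monitor who relies on the section would take a 20% loss as covered, when the tolerance is nearer 17%. The power attached to 120 is also slightly too high for the number that the plan's own assumption leaves.

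**Working it through.** **Inputs** (Sample size calculation section unless noted)
- Required total for the primary outcome: 120
- Power 80%, α=0.05. Sidedness is not stated; two-sided is assumed here.
- Effect size: d=0.30
- Predicted drop-out: 20%
- Recruitment target: 144
- Totals for the sized secondary outcomes: 56 to 84
- Allocation 1:1 (randomisation paragraph)

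**1. Reproduce the plan's figure.** Required number x (1 + drop-out) = 120 x 1.20 = 144. This matches exactly.

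**2. Number needed for the stated purpose.** Required number / (1 - drop-out) = 120/0.80 = 150, or 75 per arm. The target is 150 - 144 = 6 women lower.

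**3. What 144 leaves.** 144 x (1 - 0.20) = 115.2, about 115. That is 5 below 120, or about 4%.

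**4. Loss that 144 can absorb.** (144 - 120)/144 = 24/144 = 16.7%.

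**5. Cost in power, taking 120 at face value.** If 120 gives exactly 80% power at two-sided 0.05, the standardised effect is 1.960 + 0.842 = 2.802. With 115.2 it falls to 2.802 x √(115.2/120) = 2.745. Power is then Φ(2.745 - 1.960) = Φ(0.785), about 78.4%. The loss is about 1.6 percentage points.

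**6. Secondary outcomes.** 115 exceeds 84, the largest of their stated totals.

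**7. Does 120 itself follow from d=0.30?** For an unadjusted two-sided comparison of two equal groups, the total is 4 x 2.802²/0.30² = 31.4/0.09, about 349; rounding up each arm gives 175 + 175 = 350 (351 by the t-test). A one-sided test needs about 276. Two-sided t-test power at d=0.30 is about 37% with 120 and 36% with 115. The effect detectable with 80% power is d=0.516 with 120 and d=0.527 with 115.

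**8. Could covariate adjustment close that gap?** Bringing 350 down to 120 needs R² = 1 - 120/350 = 0.66, a baseline-outcome correlation of about √0.66 = 0.81. The section states no such assumption.

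**The case against.** The best case for leaving the text alone has four parts.

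- **The difference is trivial.** Five women and 1.6 power points change no decision about the trial. The size is as stated, and it limits how much weight the point can bear. The printed figures still disagree, and the correction costs a sentence.
- **The 20% may not apply at 6 weeks.** The primary outcome is measured at 6 weeks, but follow-up runs to 6 months, and maternal stress reactivity, one of the sized outcomes, is measured only at 6 months. If 20% is the loss by 6 months, loss at 6 weeks could be 16.7% or less and 120 would be met. The article does not settle this, so the figure of 115 is conditional on a 20% loss before the primary assessment.
- **Multiple imputation may be used.** The number analysed may therefore exceed the number observed, and the shortfall is properly one of observed outcomes. Imputation does not restore the information in 120 observed outcomes, and the section itself enlarges the target to cover drop-out.
- **The 20% could be an over-recruitment margin.** Nothing in the article supports this; it is called a drop-out rate.

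Two stronger readings are tempting. A reader might infer that the drop-out slip leaves the trial seriously underpowered. On the plan's own basis it does not: power moves from 80% to about 78%. A reader might also infer that recruiting 150 would secure 80% power at d=0.30. It would not: 150 restores 120 after a 20% loss, and 120 gives only about 37% power at that effect in a plain comparison. That gap lies in the step from d=0.30 to 120, before drop-out enters.

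**Conclusion.** The point holds as an arithmetic error of small size. Under its own 20% prediction, the target of 144 leaves about 115 observed primary outcomes against the 120 called necessary; it covers a loss of up to 16.7%.

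This rests on three assumptions: the 20% is a share of women recruited, it is lost before the 6-week assessment, and 120 is accepted as giving 80% power. The sized secondary outcomes are not affected. The failure of 120 to follow from d=0.30 is a separate and larger matter in the same paragraph. It is noted here because it constrains how this correction can be worded.

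**What to change.** Keep 144 and change the closing sentence of the Sample size calculation section in one of two ways:

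- State that with 144 recruited and 20% lost before 6 weeks, about 115 women are expected to have primary-outcome data, with power of about 78% instead of 80% on the plan's own basis.
- Replace the 20% with an allowance of up to 16.7%, for which 144 yields 120. The 20% must then come out; leaving both figures keeps the contradiction.

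Either version should name the visit to which the loss applies.

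If a detectable effect is quoted for 115 (about d=0.53, unadjusted two-sided test, 80% power), it must replace the d=0.30 statement and give those assumptions. Placed beside d=0.30, it would put an unexplained conflict in the same paragraph.

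The cost is one sentence and a slightly less favourable figure, with no extra recruitment and no change to randomisation or analysis. The correction does not make 120 or 150 adequate for d=0.30; the basis for 120 needs its own explanation or revision.

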## Patient and public involvement

The acceptability of the intervention was assessed by participants during the previous proof-of-principle RCT.^4^ A questionnaire of satisfaction and acceptability examined the burden of the intervention. An individual feedback and debriefing session will be offered to each participant. Results will be disseminated in written form to the participants and distributed to the public via social media and public events. They will also be discussed with clinical professionals involved in this project.

## Data management and statistical analyses

All study data will be entered by research staff. Study data will be managed using Research Electronic Data Capture (REDCap) tools hosted at Lausanne University Hospital.^131 132^ REDCap is a secure, web-based software platform designed to support data capture for research studies. Double data entry will be done for the primary outcomes. For the rest of the data, a random 5% will be double checked. Access to the full final trial dataset will be restricted to the principal investigator.

For the primary analyses, group differences regarding the mean subscale and total scores of the PCL-5 and CAPS-5 at 6 weeks will be analysed using separate linear regression analyses. Analyses will be adjusted for recruitment centre and the respective baseline values. Associations between primary outcomes and potential confounders, such as maternal and gestational age, will first be assessed applying univariate tests. Subsequent analyses will be adjusted for significant covariates. For secondary aims, the analyses will be performed for differences in changes between groups and differences between groups at different time points in maternal and infant outcomes. Proportion of participants meeting the diagnostic criteria for PTSD at 6 weeks and 6 months between the two groups will also be compared using logistic regression analyses. The same procedure for identifying significant covariates described above will be applied here. Furthermore, post hoc exploratory analyses will be conducted but described as such in publications. All regression analyses regarding cortisol data will be adjusted for potential covariates, such as cosleeping, breastfeeding, menstrual cycle, and infant and maternal medication. For HRV analyses, interbeat intervals from baseline, stress task and recovery will be analysed by the extraction from ECG recordings. Statistical parameters of HRV^133^ will be calculated using Kubios HRV Analysis V.2.2 software.^134^ Time domain measures and spectral frequency measures will be used for calculations. Multiple imputation methods will be used to manage missing data, if appropriate.

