### Primary outcome

The primary outcomes are differences in the presence and severity of maternal PTSD symptoms between the intervention and the attention-placebo control group at 6 weeks post partum measured with the Clinician-Administered PTSD Scale (CAPS-5)^100 101^ and the PTSD Checklist (PCL-5) for DSM-5.^102^

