#### Psychological vulnerability

CAPS for DSM-5 *(*CAPS-5):^100 101^ The CAPS-5 assesses presence and severity of PTSD symptoms and diagnosis based on the DSM-5.^2^ This gold-standard instrument contains 20 items referring to the four symptom clusters, as well as 10 items referring to symptoms duration, distress or impairment, global ratings and dissociative subtype. Each diagnostic criterion is rated from 0=absent to 4=extreme/incapacity in function of symptoms intensity and frequency with a diagnostic cut-off equal to 2. The CAPS-5 has demonstrated good psychometric proprieties.^100^ In the absence of a French version at the time when the study was designed, a forward–backward method was executed to realise a translation and cultural adaptation.^103^

The PCL for DSM-5 (PCL-5):^102^ This 20-item self-report questionnaire measures symptoms of PTSD over the past month and is used to assess frequency of PTSD symptoms. The PCL-5 refers to the four symptoms clusters of PTSD and scales on a 5-point scale with 0=not at all and 4=extremely. Scores are summed to create a total symptom severity score.^104^ The French version of the PCL-5 demonstrated strong reliability and validity.^105^

Trauma-related intrusive memories diary:^4^ Intrusive memories of birth-related trauma experienced during the 7 days following ECS are reported in a daily diary, adapted from previous work,^4^ to assess the frequency of intrusive memories of the trauma . For each intrusion, the time, content and type (intrusive memory, nightmare or other) are recorded, as well as the level of distress on a 5-point scale with ratings of 0=not at all to 5=extremely.

ASD Scale:^106^ This self-assessment instrument measures frequency of ASD symptoms over the last week and is based on DSM-5.^107^ Each of the 19 items is scored using a scale from 1=not at all to 5=extremely, with a higher score indicating higher ASD symptoms. Good sensitivity and specificity has been reported.^106^ The forward–backward method was executed to realise a French version translation and cultural adaptation.^103^

Anxiety subscale of Hospital Anxiety and Depression Scale:^108^ This self-report questionnaire measures severity of anxiety symptoms during the last week. The anxiety subscale consists of 7 items scored on a 4-point scale (0=never, 3=most of the time). Higher scores indicate higher distress. Good psychometric properties have been reported for the French version.^109^

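### Ten regressions on two instruments are labelled primary, but the trial is sized for one primary outcome at an undivided 0.05 and the article names no deciding score

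*Protocol article*

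**What the plan says.** All references are to the protocol article.

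- **Primary outcome** uses the plural: "The primary outcomes are differences in the presence and severity of maternal PTSD symptoms". It names CAPS-5 and PCL-5 side by side, at 6 weeks, without ranking them.
- **Data management and statistical analyses**, on what is analysed as primary: "group differences regarding the mean subscale and total scores of the PCL-5 and CAPS-5 at 6 weeks will be analysed using separate linear regression".
- **Psychological vulnerability** (Measures) gives the cluster structure. Of CAPS-5: "This gold-standard instrument contains 20 items referring to the four symptom clusters". Of the other instrument: "The PCL-5 refers to the four symptoms clusters of PTSD".
- **Sample size calculation** speaks of one outcome. It presents 120 women as sufficient "to have 80% power (α=0.05) to detect a between-group difference of d=0.30 of the primary outcome", identified there as PTSD symptoms at 6 weeks.
- On presence and diagnosis, the Abstract, the strengths and limitations list, Aims of the present study and Primary outcome all make presence part of the primary outcome. Sample size calculation lists diagnosis among the "maternal secondary outcomes (PTSD diagnosis, ASD symptoms and physiological stress reactivity". The analysis section, after turning to the secondary aims, says: "Proportion of participants meeting the diagnostic criteria for PTSD at 6 weeks and 6 months between the two groups will also be compared", by logistic regression.

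**The concern.** A trial read at 5% needs to say which result decides it. Here every cluster score and total on two instruments carries the primary label, each with its own regression. The article does not say whether one significant score is enough, whether both instruments must agree, or which instrument prevails if they differ. Any of ten results could then be reported as the primary finding, with a chance of a false positive well above the 0.05 used to size the trial.

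Presence adds a second difficulty. It is in the primary definition, but all the analyses labelled primary are linear regressions on scores. If presence means diagnosis, the article gives it two ranks. If it means something else, no analysis is stated for it.

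**Working it through.** **1. The plan's own figure.** The only error and power statement for the primary outcome is 120 women, d = 0.30, 80% power, α = 0.05.
- Two-sided, normal approximation: n per arm = 2(1.960 + 0.842)²/0.30² ≈ 175, or 350 in total. One-sided: 138 per arm, or 276.
- The stated 120 is not reproduced. Power at 60 per arm is 38% two-sided and 50% one-sided.

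That is a separate problem. What matters here is that the calculation covers one outcome and does not divide alpha.

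**2. Number of tests labelled primary.** 2 instruments × (4 clusters + 1 total) = 10.

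**3. Ceiling if the tests were independent.** 1 − 0.95¹⁰ = 0.401. For two totals, 1 − 0.95² = 0.0975.

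**4. Allowing for correlation.** The article gives no correlations between scores, so these are assumptions. Eight cluster scores were simulated under no effect as correlated normal test statistics, 400,000 draws per setting. Each total was formed from its four clusters with weights 5, 2, 7 and 6. These sum to the 20 items, but the split is an assumption. Each test was two-sided at 0.05.

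| Within instrument | Across, different cluster | Across, same cluster | Any of 10 significant | Any significant in favour of intervention | Either total significant |
|---|---|---|---|---|---|
| 0.2 | 0.1 | 0.4 | 32.9% | 17.0% | 9.3% |
| 0.5 | 0.3 | 0.5 | 27.0% | 13.6% | 8.9% |
| 0.5 | 0.4 | 0.6 | 25.7% | 12.9% | 8.3% |
| 0.6 | 0.5 | 0.7 | 22.8% | 11.4% | 8.0% |
| 0.7 | 0.6 | 0.75 | 19.8% | 10.0% | 7.7% |
| 0.8 | 0.7 | 0.8 | 16.8% | 8.4% | 7.5% |
| 0.9 | 0.8 | 0.85 | 13.4% | 6.7% | 7.3% |

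For comparison, one two-sided test at 0.05 gives 5% in either direction and 2.5% in favour of the intervention.

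**5. Cross-check of the last column.** Under these weights the correlation between totals is (114·r_same + 286·r_diff)/(114 + 286·r_within), where 114 = 25 + 4 + 49 + 36 and 286 = 20² − 114. The 0.6 row gives (79.8 + 143.0)/285.6 = 0.78. The bivariate normal probability that at least one of two such tests exceeds 1.96 in size is 7.9%, which agrees with the simulated 8.0%.

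**6. What an explicit rule would cost.** With 60 per arm and 80% power, the detectable effect is (z₁₋α/₂ + 0.842)·√(2/60):
- one primary at 0.05: 2.802 × 0.1826 = 0.51;
- two totals at 0.025 each: 3.083 × 0.1826 = 0.56;
- ten tests at 0.005 each: 3.649 × 0.1826 = 0.67.

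**The case against.** **An adjustment may exist elsewhere.** The analysis plan is not shown, and a testing order or multiplicity rule is commonly placed there. This stands: a reader might infer that the trial has no error control, but the document supports only that this article states none. It does not remove the point, because the article is not merely silent. It labels ten analyses primary and sizes the trial for one.

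**The percentage is not a property of the trial.** This stands too. A reader might take 20% to 26% as the trial's false-positive rate. It follows only from assumed correlations of 0.7 to 0.5 and counts significance in either direction. Nor does the article promise a familywise 5%: its 0.05 is an input to the power calculation and is also used for secondary outcomes. Most of the excess comes from the subscales.

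**Presence is not an eleventh primary test.** A reader might count it as one. The wording is presence of PTSD symptoms, and the CAPS-5 description lists presence and severity of symptoms as well as diagnosis. Diagnosis is treated as secondary in both the sample size and analysis sections, so those two agree. What remains is a primary component with no matching primary analysis, or a conflict if presence is meant as diagnosis.

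**Blinding.** It may be tempting to add that PCL-5 is self-reported by women who know which task they did. The article says participants are blind to allocation and calls both conditions simple tasks. In any case, this does not bear on the number of tests.

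**Conclusion.** The point holds in this form: ten regressions are fixed as primary, two instruments are named as primary without ranking, and the sample size assumes one outcome at an undivided 0.05. Which result decides the trial belongs in the protocol, and the current text settles it badly.

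If each test is read at 0.05, the chance of at least one significant primary result under no effect is about 13% to 33% for within-instrument correlations of 0.9 to 0.2, with 40% as the value under independence. A false claim of benefit is about half as likely, roughly 7% to 17%. Restricting the primary analysis to the two totals brings the either-direction figure to 7% to 9%. All these figures rest on assumed correlations and on no adjustment being applied; only the count of ten comes directly from the document. The status of presence and diagnosis is an inconsistency to reconcile and is not included in these figures.

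**What to change.** Before unblinding:

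1. Name the deciding score. One option is CAPS-5 total severity at 6 weeks, two-sided 0.05, since the article itself calls that instrument the gold standard, with PCL-5 total tested only if CAPS-5 is significant. An alternative that keeps both instruments is to test the two totals with alpha split between them, for example 0.025 each.
2. Move the subscale scores of both instruments to secondary outcomes, reported as estimates with 95% intervals.
3. State what presence means, and give it and PTSD diagnosis the same rank in the Abstract, the strengths and limitations list, Aims, Primary outcome, Sample size calculation and the analysis section.
4. Make the sample size statement refer to the named score and to the alpha at which it is tested.

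The cost is wording, with no new data. A result seen only on a subscale, or only on the lower-ranked instrument, would no longer count as a primary success. Splitting alpha avoids ranking the instruments but raises the detectable effect at 60 per arm from about 0.51 to 0.56.
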